### Participant timeline and recruitment

Before the screening, the informed consent form will be verbally explained to all participants. Written informed consent will be acquired from all patients prior to their participation in this study. After enrolment, the baseline characteristics of the participants will be measured preoperatively. Surgery will be performed within 7 days of enrolment. Adjuvant chemotherapy will be considered according to the National Comprehensive Cancer Network (NCCN) guidelines. The first two follow-up visits will be scheduled at one month and three months postoperatively, then every three months for the first two years and every six months for the next three years. This trial is scheduled to last for 96 months and the recruitment started on April 8, 2021. Recruitment advertisements for the study will be posted on notice boards in participating centres. The CSILS flowchart was designed based on consolidated standards of reporting trials (CONSORT 2010 Flow Diagram, Fig. 1). The study schedule is shown in Table 3.

**Fig. 1 Fig1:**
[figure not shown]
CSILS Flow Diagram

**Table 3 Tab3:**
[figure not shown]
Study schedule

*POD* Postoperative day, *M* Month, *SILS* Single-incision laparoscopic surgery, *CLS* Conventional laparoscopic surgery, *VAS* Visual analogue scale, *CT* Computed tomography, *MRI* Magnetic Resonance Imaging, *EKG* Electrocardiogram, *QLQ-C30* Quality of Life Questionnaire-Core 30, *QLQ-CR29* Quality of Life Questionnaire-Colorectal 29, *EORCT* European Organization for Research and Treatment of Cancer

^a^ Laboratory tests include routine blood tests, liver and kidney function tests, electrolytes tests, and coagulation tests

^b^ These examinations are optional depending on the patient's condition

### Interventions

Preoperative nutritional support, bowel preparation, prophylactic systemic antibiotics, prophylactic anticoagulation, respiratory function training, and prophylaxis for other potential high-risk complications are administered according to the patient's condition and the routine of each study centre. Nasogastric tubes will not be routinely used.

Radical resection (R0) based on the same oncological principles is required for all operations. The principles include adequate surgical resection margins, complete or total mesocolic excision (CME/TME), and D3 lymph node dissection. Intraperitoneal operations must be performed using laparoscopic instruments supported by a camera system. In the SILS group, the operations will be performed through a single incision, usually with a transumbilical approach. A single port device and laparoscopic instruments will be placed through the small incision. In the CLS group, the operation will be performed with 3 to 5 trocars. Conventional laparoscopic instruments, precurved instruments, articulating instruments, 3D laparoscopes, and flexible laparoscopes, among others., may be used during the operation. Intestinal segment mobilization, lymph node dissection, and vascular ligation should be performed under laparoscopy. The specimen excision and the anastomosis will be allowed to be performed in an open state using an auxiliary small incision (usually the same size as the tumour). Auxiliary incisions will generally be limited to one, except in cases where a stoma is needed. According to the site of the tumour, appropriate surgical methods, including right colectomy, left colectomy, sigmoidectomy, and anterior resection, will be selected. Prophylactic ileostomy will be performed when necessary. Placement of drainage tubes will be decided by the surgeons. Unedited video recordings of the laparoscopic operations, photographs of the incisions, and photographs of the specimens will be documented.

The treatment strategy will be required to change (SILS to additional trocar/laparotomy; CLS to laparotomy) if one of the following happens: intractable intra-abdominal haemorrhage, severe organ damage, other serious or life-threatening complications related to surgical procedures or carbon dioxide pneumoperitoneum, or other technical or instrumental factors requiring conversions. When the length of the auxiliary incision is larger than 10 cm, conversion to laparotomy will be considered.

### Primary endpoint

The primary endpoint is 3-year disease-free survival (DFS) measured at 36 months postoperatively. DFS will be calculated from the time of surgery to the time of tumour recurrence or death from tumour reasons (in the case of an unknown tumour recurrence date). If neither death nor tumour recurrence is observed during the follow-up, the final date of confirmation of disease-free survival will be marked as the date of the latest outpatient visit or the examination received. Recurrence will be confirmed by radiological or histological methods.

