### Objective and hypothesis

This study will investigate the long-term oncologic outcomes of SILS compared to CLS for CRC. The hypothesis is that the oncologic outcomes of SILS for CRC are noninferior to CLS.

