### Sample size calculation

In this study, the 3-year DFS is the main effectiveness evaluation index for noninferiority evaluation. According to previous studies [27–29], the 3-year DFS of the CLS group was approximately 75%. This study assumes that the 3-year DFS of the study group is the same as that of the control group. The expected enrolment time is 3 years, and the follow-up time to reach the primary endpoint is 3 years. If the acceptable noninferiority limit of DFS in the three years of this study is 10%, when DFS is exponentially distributed, the corresponding HR limit is 1.49. This number will be combined with "Log-Rank Tests for Noninferiority" in the professional sample size estimation software NCSS-PASS (14th edition, NCSS, LLC, Utah, USA). When the unilateral statistical significance level is 0.025, the inspection efficiency is 80%, and the study group and the control group will be allocated in the ratio of 1:1, the required sample size of each group will be 284. Considering that the largest abscission rate in this clinical study is approximately 20%, it was finally determined that the sample size of each group will be 355 cases, and the total number of cases required will be 710.

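### The primary endpoint is called disease-free survival but counts only recurrence or tumour death; non-tumour deaths are not events and have no defined handling

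*Protocol article*

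**What the plan says.** The Primary endpoint section sets the endpoint as "3-year disease-free survival (DFS) measured at 36 months postoperatively". The event rule is: "DFS will be calculated from the time of surgery to the time of tumour recurrence or death from tumour reasons". A parenthesis limits the tumour-death part to use "in the case of an unknown tumour recurrence date". The next sentence fixes the last disease-free date, and opens: "If neither death nor tumour recurrence is observed during the follow-up". Here death carries no cause.

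The Objective section reads: "The hypothesis is that the oncologic outcomes of SILS for CRC are noninferior to CLS". The Sample size calculation takes as its planning rate that "the 3-year DFS of the CLS group was approximately 75"%, and assumes that "the 3-year DFS of the study group is the same as that of the control group". It sets the margin: "the acceptable noninferiority limit of DFS in the three years of this study is 10"%, with a corresponding hazard ratio limit of 1.49. The Statistical methods section tests noninferiority on 3-year DFS only, by comparing confidence intervals of survival rates.

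Deaths of any cause enter elsewhere: early mortality and 3- and 5-year overall survival under Secondary endpoint, and expedited reporting with a 3% per-centre rule under Adverse events.

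**The concern.** Disease-free survival normally fails at recurrence or death from any cause. Under the event rule here, a patient who dies of an anastomotic leak, sepsis or a cardiac event without recurrence has not failed. That patient does not meet the condition of the censoring sentence either, because a death was observed. Two analysts could code the same death differently, and the article would not settle which is right.

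Three features of this trial make the point matter.

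- The Discussion describes SILS as technically more demanding than conventional laparoscopy. Eligibility reaches age 85 and ASA class III. Some non-tumour deaths are foreseeable, and a difference between arms is a legitimate question.
- The trial is open-label, so whether a death was from the tumour is judged with the arm known. Death from any cause needs no such judgement.
- If these deaths are censored, the Kaplan–Meier estimate treats the patients as still able to recur. Death without recurrence is a competing event, not ordinary loss to follow-up.

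**Working it through.** **1. The two sentences side by side.**

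| Patient | Event rule | Censoring sentence |
|---|---|---|
| Recurrence | event | does not apply |
| Tumour death, recurrence date unknown | event | does not apply |
| Alive, no recurrence | no event | applies |
| Non-tumour death, no recurrence | no event | does not apply |

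The last row has no home.

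**2. The plan's own sample size.** Inputs from the Sample size calculation: 75% in both arms, HR limit 1.49, one-sided 0.025, 80% power, 3 years' accrual plus 3 years' follow-up, 20% dropout.

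- Events: 4 × (1.960 + 0.842)² / (ln 1.49)² = 197.4.
- Hazard: −ln(0.75)/3 = 0.0959 per year. Event probability with uniform accrual: 1 − (0.75 − 0.5625)/0.2877 = 0.348.
- Per group: 197.4 / 0.348 / 2 = 283.5, so 284. After dropout: 284/0.8 = 355. Total: 710.

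The stated figures reproduce. The issue is the event definition, not the arithmetic.

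**3. Illustration at the margin.** The documents give no non-tumour death rate, so the excess is assumed. Let true all-cause 3-year DFS be 75% v 65%, let 1 or 2 of the 10 points be excess non-tumour deaths in SILS, and let those deaths be left out of the endpoint. The measured deficit d is then 9 or 8 points.

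P(noninferiority) = Φ((0.10 − d)/SE − 1.96), with SE² = [0.75 × 0.25 + (0.75 − d)(0.25 + d)]/n.

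| d | n = 284 | n = 355 |
|---|---|---|
| 0.10 | 2.5% | 2.5% |
| 0.09 | SE 0.0381, 4.5% | SE 0.0341, 4.8% |
| 0.08 | SE 0.0379, 7.6% | SE 0.0339, 8.5% |

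**4. Sensitivity to the deaths themselves.** Assume tumour-only DFS of 75% in both arms, 2% non-tumour death in CLS, a further x in SILS, and 284 per arm. All-cause DFS is 0.75 × 0.98 = 73.5% in CLS and 0.75 × (0.98 − x) in SILS.

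| x | Extra deaths | All-cause loss (points) | P(noninferiority), all-cause | P(noninferiority), endpoint as defined |
|---|---|---|---|---|
| 1% | 3 | 0.75 | 70% | 79% |
| 2% | 6 | 1.5 | 62% | 79% |
| 3% | 9 | 2.25 | 54% | 79% |
| 5% | 14 | 3.75 | 38% | 79% |

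The last column does not move.

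**5. The basis of the 75%.** The article does not say whether it is an all-cause or a tumour-only rate. If it is all-cause and 2–5% of patients die of other causes (assumed), the tumour-only control rate c is higher. Adding the deaths back directly gives c = 77–80%. Treating them as independent censoring gives 0.75/0.98 = 76.5% to 0.75/0.95 = 78.9%. The hazard ratio that a 10-point margin tolerates is ln(c − 0.10)/ln(c):

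- c = 76.5% gives 1.52, and 78.9% gives 1.57.
- c = 77% gives 1.53, and 80% gives 1.60.

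The range is therefore 1.52–1.60, against the stated 1.49.

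**6. Effect of counting all deaths.** Suppose instead that 75% is tumour-only, and that non-tumour death by 3 years is equal in both arms. The 10-point margin is kept, with the HR limit recomputed unrounded.

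| Non-tumour death | All-cause DFS | n per group (after dropout) | Power at 284 |
|---|---|---|---|
| 0% | 75.0% | 277 (347) | 81.0% |
| 2% | 73.5% | 283 (354) | 80.2% |
| 4% | 72.0% | 289 (362) | 79.3% |
| 6% | 70.5% | 295 (369) | 78.6% |
| 8% | 69.0% | 300 (375) | 77.9% |

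The 0% row differs from 284 only because the limit is 1.497 before rounding.

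**The case against.** The best defence is the hypothesis itself, which concerns oncologic outcomes. A tumour-specific endpoint can answer that question, and against that estimand the error rate at the margin stays nominal. This stands as far as it goes. But the endpoint is labelled disease-free survival, and the defence leaves non-tumour deaths without a rule.

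A second defence is that competing deaths are commonly dealt with in the full protocol or analysis plan, which are not shown. That would excuse silence on detail. It does not excuse an event definition that, as printed, leaves these deaths out.

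A reader might also infer more than the text supports:

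- *That the two sentences contradict each other.* They do not. One lists events and the other dates the patients who had none; a non-tumour death falls between them.
- *That non-tumour deaths will be censored.* The article does not say so. The illustrations assume they are left out of the endpoint, which follows from the event rule but is not spelled out.
- *That a harm of SILS would be hidden.* It would be missed by the primary test, not by the trial. Early mortality, overall survival at the same 3-year point and safety reporting would show it.
- *That 4.5–8.5% is the plan's false-positive rate.* It requires a true all-cause deficit exactly at the margin plus an assumed excess of non-tumour deaths. Likewise, the losses in step 4 all lie inside the 10-point margin: they show insensitivity, not false claims.
- *That the margin has loosened to 1.52–1.60.* This holds only if the 75% is all-cause and the difference in rates governs. If the stated HR limit of 1.49 governed, it would not move.

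**Conclusion.** The point holds in this form: as printed, the primary event excludes operative, treatment-related and other non-tumour deaths, and the article assigns them no handling. The noninferiority test does not respond to them, and applying the definition needs an open-label judgement of cause of death. The secondary and safety outcomes that would show such deaths have no stated margin and do not condition the noninferiority claim.

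Confidence in the reading of the text is high. The size is conditional. It rests on an assumed excess of 1–2 points, roughly 3 to 7 deaths per arm (0.01 × 284 = 2.8; 0.02 × 355 = 7.1), and on an unknown basis for the 75%. Because this is the primary event of a noninferiority trial, it should be settled before analysis even if the eventual effect is small.

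**What to change.** Before any comparative data are seen, amend the protocol and analysis plan as follows.

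1. Define the event for both 3-year and 5-year DFS as the first of confirmed recurrence or death from any cause.
2. Censor only patients alive without recurrence, at their last disease assessment.
3. Keep the tumour-only definition as a secondary or sensitivity analysis, with non-tumour death as a competing event.
4. State whether the 75% planning rate is all-cause or tumour-only.

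No new data are needed, since deaths are already collected for overall survival. The cost is more than a change of wording: recruitment started on April 8, 2021, so this is a formal amendment to the primary endpoint of an open-label trial under way. If the 75% is all-cause, the planned 284, 355 and 710 stand. If it is tumour-only, power at 284 per group is about 78–80% for 2–8% non-tumour death. That loss should be restated rather than met by enrolling more patients.

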### Eligibility criteria

Patients between 18 and 85 years old, of both sexes, with cT1-4aN0-2M0 CRC diagnosed via computed tomography (CT) and/or colonoscopy according to the 8th Edition of the American Joint Committee on Cancer (AJCC) Cancer Staging Manual, with a tumour located above the peritoneal reflection and a tumour size no larger than 5 cm will be further screened for inclusion. Table 2 shows the detailed inclusion, exclusion, and withdrawal criteria.

**Table 2 Tab2:** Inclusion, exclusion, and withdrawal criteria

Inclusion criteria	Exclusion criteria	Withdrawal criteria
• 18 years < age < 85 years • Pathological colorectal adenocarcinoma • Tumor located in colon and rectum (the lower border of the tumor is above the peritoneal reflection) • Clinically diagnosed cT1-4aN0-2M0 lesions according to the 8th Edition of AJCC Cancer Staging Manual without preoperative neoadjuvant therapy performed • Tumor size of ≤ 5 cm • Performance status ECOG 0–1 • ASA class I to III • Informed consent	• BMI > 35 kg/m2 • Previous gastrointestinal surgery (except for appendicectomy) • Emergency operation due to complication caused by colorectal cancer (bleeding, perforation or obstruction) • Multiple malignant lesions • Familial adenomatous polyposis (FAP) or Inflammatory bowel disease (IBD) • Requirement of neoadjuvant therapy • Pregnancy or lactation • Severe mental disease • Severe liver and kidney dysfunction, coagulation dysfunction, or with serious comorbidities that cannot perform surgery • Requirement of simultaneous surgery for other disease • Other malignant disease history within 5 years	• Intraoperative or pathological confirmation of invasion of adjacent structures requiring combined organ resection or distant metastasis • Non-colorectal adenocarcinoma confirmed by postoperative pathology • Multiple malignant lesions confirmed by postoperative pathology • Requirement of emergency operation due to the change of illness state • Inability to undergo surgery or anesthesia due to the change of illness state • Receive treatment other than the protocol during the treatment period (except for treatment of tumor recurrence and metastasis) • Patient required to withdraw • Unable to complete the clinical trial due to various reasons • Treatment implemented is proven to violate the study protocol

*BMI* Body mass index, *ASA* The American Society of Anesthesiologists, *ECOG* Eastern Cooperative Oncology Group

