### Randomization and blinding

This will be an open-label trial. Surgical procedures and postoperative intervention will not be concealed from patients or investigators. The participants will be randomly assigned to either the CLS or SILS group at a 1:1 ratio using a central, dynamic, and stratified block randomization method. The control factors include age, preoperative stage, and planned surgical intervention. An investigator from each centre will fill in the information of every participant through the network, and the central random system will analyse the information and give the random number and grouping.

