### Statistical methods

SAS 9.4 statistical software will be used to perform the statistical analyses. The noninferiority analysis for the primary endpoint of 3-year DFS will be conducted by comparing 95% confidence intervals of survival rates between the test and control groups on a modified intent-to-treat (MITT) population basis. Baseline data and validity analyses will be conducted on a modified intent-to-treat (MITT) basis. The primary endpoint will also be analysed on a per-protocol (PP) basis, with the MITT analysis results prevailing. Safety evaluation, including laboratory test data, will be conducted in the safety analysis population (SAP). There is no planned interim analysis for the 3-year DFS rate. Continuous data will be described as the means with standard deviations or medians with interquartile ranges, and categorical data will be expressed as frequencies and percentages. Comparisons between groups will be conducted using the Wilcoxon rank-sum test, Student’s t test, Pearson χ2 test, and Fisher exact test, as appropriate. Survival data will be analysed using the Kaplan–Meier method and log-rank test. A general linear model for quantitative indicators, logistic regression for qualitative indicators, and Cox's proportional hazards model for survival data will be used to assess the effects of baseline, treatment, centre, and treatment-by-centre interactions. A two-sided *p* value < 0.05 will be considered statistically significant.

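### Disease-free survival is counted from surgery rather than randomisation, so randomised patients who are never operated on have no time zero in the primary comparison

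*Protocol article*

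**What the plan says.** Under Primary endpoint, the protocol article sets the origin of the endpoint, "DFS will be calculated from the time of surgery to the time of tumour recurrence or death from tumour reasons", and its reading time, "The primary endpoint is 3-year disease-free survival (DFS) measured at 36 months postoperatively". Both are tied to the operation.

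The sequence before the operation comes from other sections:

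- Participant timeline and recruitment: "Surgery will be performed within 7 days of enrolment".
- Randomization and blinding: "The control factors include age, preoperative stage, and planned surgical intervention". Preoperative stage and a planned procedure are known before the operation, so allocation comes before it.
- The same section on openness: "Surgical procedures and postoperative intervention will not be concealed from patients or investigators".
- Eligibility criteria, Table 2, withdrawal column: "Inability to undergo surgery or anesthesia due to the change of illness state" and "Patient required to withdraw". The plan therefore expects that some enrolled patients may not reach surgery.

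Statistical methods places the primary noninferiority analysis "on a modified intent-to-treat (MITT) population basis" and lets that result prevail over the per-protocol one. No section gives a second time origin, or says how a randomised patient without an operation enters the DFS analysis.

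**The concern.** Surgery happens after randomisation. If the endpoint clock starts there, having an operation becomes a condition for having an outcome at all. A randomised patient who is never operated on has no start date, so no DFS time can be calculated from the stated definition. The groups compared are then those randomised and operated on, which need not be those that randomisation created.

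In most surgical trials this costs little. It deserves attention here because patient and investigator know the arm before the operation, and because the trial tests noninferiority. If patients with a poor outlook fall out of one arm more than the other, the difference between arms shifts. A shift that flatters SILS makes noninferiority easier to declare; one that flatters CLS makes it harder.

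**Working it through.** **Inputs from the protocol article (Sample size calculation).** 3-year DFS 75% in both arms; margin 10 points, given as HR 1.49; one-sided alpha 0.025; power 80%; 3 years of enrolment and 3 years of follow-up; 20% dropout; 284, then 355 per group, 710 in total. From Participant timeline and recruitment: up to 7 days from enrolment to surgery.

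**Assumed, because the article gives no figures.** The share *u* of an arm that is never operated on (1% to 3%), and the proportion *f* of those patients who would fail by 36 months (50% to 100%).

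**1. The plan's own figure.**

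- Events = 4 × (1.96 + 0.84)² / (ln 1.49)² = 197.4.
- Yearly hazard = −ln(0.75)/3 = 0.0959.
- Event probability with uniform 3-year accrual and 3 years of further follow-up = 1 − [exp(−0.0959 × 3) − exp(−0.0959 × 6)] / (0.0959 × 3) = 0.348.
- 197.4 / 0.348 / 2 = 283.5, so 284 per group; 284 / 0.8 = 355; total 710.

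The stated size reproduces. Nothing in it depends on a shift of origin by a few days.

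**2. Operated patients: effect of moving the origin.** At the planned hazard, 7 days changes 3-year DFS by

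0.75 × [1 − exp(−0.0959 × 7/365.25)] = 0.75 × 0.00184 = 0.0014, or 0.14 points.

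This is an upper limit if the 7-day window is kept and allocation does not precede enrolment. It applies to both arms, so it nearly cancels in the difference.

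**3. Never-operated patients: loss in one arm only.** Let DFS among the operated be 75%. The rate among all randomised patients in that arm is (1 − u) × 0.75 + u × (1 − f). The overstatement is

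0.75 − [(1 − u) × 0.75 + u × (1 − f)] = u × (f − 0.25).

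| u | Patients of 355 | f = 50% | f = 100% |
|---|---|---|---|
| 1% | 4 | 0.25 points | 0.75 points |
| 3% | 11 | 0.75 points | 2.25 points |

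**4. Loss in both arms.** The bias in SILS minus CLS is u_S × (f_S − 0.25) − u_C × (f_C − 0.25).

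- All unoperated patients fail, 3% lost in SILS and 1% in CLS: 0.75 × (3 − 1) = 1.5 points towards noninferiority.
- The same rates with the arms exchanged: 1.5 points against noninferiority.
- 3% in each arm with equal prognosis: 0.

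**The case against.** The strongest reply is that few patients are affected and that they are probably spread evenly. Both arms are laparoscopic resections under the same oncological principles and are due within a week of enrolment. Nothing in the article suggests that patients become unfit for surgery more often in one arm. This stands, and it is why the size is described as probably small.

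A second reply is that the article does not define its modified intention-to-treat set, and that the handling of unoperated patients may be settled in the full protocol or analysis plan. The missing definition is indeed no fault of an article. The time origin, however, is stated. Even if the set held every randomised patient, an unoperated one would have no start date unless another document overrode this definition.

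Three stronger readings are tempting and are not supported:

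- A reader might infer that anyone who postpones or refuses the allocated operation loses a start date. The definition refers to surgery, not to the allocated surgery. A late operation, or the other operation, still supplies a date. If such patients were removed, it would be through the withdrawal list or the analysis set, not through the clock.
- A reader might infer that the bias favours SILS. That requires greater loss of poor-prognosis patients from SILS than from CLS, and the article gives no non-operation rate for either arm.
- A reader might infer that the article expressly excludes unoperated patients from analysis. It does not; their loss follows from the origin.

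A final reply is that moving the clock is not enough by itself. The event is recurrence or tumour death, and a tumour that was never resected cannot recur. This is correct, and the remedy needs a rule for it.

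**Conclusion.** The point holds in a narrow form. The stated origin leaves randomised, never-operated patients without a primary outcome time, in a trial where the arm is known before the operation. For everyone who is operated on, the choice of origin is worth at most about 0.14 points and can be ignored.

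For the never-operated, loss confined to one arm overstates that arm's 3-year DFS by 0.25 to 2.25 points of the 10-point margin. The upper end needs 3% lost from one arm, none from the other, and every lost patient failing. The direction is towards noninferiority if the loss is in SILS and against it if in CLS; equal loss with equal prognosis leaves no bias. All these rates are assumptions. The case for change is therefore not that a large bias is expected, but that an avoidable selection after randomisation can be removed from the primary endpoint at little cost.

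**What to change.** In the Primary endpoint section:

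1. Count DFS from the date of randomisation for every randomised patient, whether or not an operation took place, and read the 3-year rate at 36 months from randomisation. Use the same origin for OS.
2. State in advance how a patient whose tumour was never resected is counted for DFS: for example, as an event at time zero, with the alternative as a sensitivity analysis.
3. Keep the surgery-date origin as a sensitivity analysis.
4. Report never-operated patients by arm, with reasons.

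The central allocation system should already hold the randomisation date. The cost is the changed wording, one added event rule, and outcome follow-up for a few unoperated patients: about 4 to 11 per arm at the assumed 1% to 3%. The sample size stays at 284 per group before dropout, 355 after it, and 710 in total.
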